## Discussion

MDD is responsible for the highest burden of disease of any non-fatal disease worldwide, but its etiological mechanisms remain unclear and we are unable make the correct diagnosis and provide effective treatment with consistency. PROUD aims to accelerate homeostatic and precision medicine by establishing a prospective cohort study. This study has two significant strengths. (1) It will recruit a large, multidimensional cohort representative of the Chinese population: a total of 14,000 patients will be included, recruited from 52 tertiary hospitals across 24 provinces and cities in China. Furthermore, multimodal data will be collected, including clinical phenotypes, multi-omics, neuroimaging, neurophysiology and digital phenotypes. (2) This study will track mood changes and investigate the progression of MDD. External visits will be scheduled automatically whenever certain criteria are met and will be able to capture the patients' mood swings.

The present study will develop standard operating and quality control procedures for the collection of multidimensional data, and construct a data platform to ensure standardization and shareability of data. Data from multidimensional sources will be integrated into a central data platform, thus aiding the management and future application of the data.

It is clear that this study may also encounter certain difficulties. In response to the Corona Virus Disease 2019 (COVID-19), we have made the “Emergency Plan for Prevention and Control of Novel Coronavirus Pneumonia Outbreak”. If an outbreak strikes, we will actively coordinate resources, prioritize the security of the patients and researchers and try to minimize the impacts on progress while maintaining the quality of the study.

In conclusion, the PROUD study will construct and provide a comprehensive database that will facilitate further analyses and studies and the development of homeostatic and precision medicine in China.

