## Introduction

Homeostasis refers to a state in which the organism maintains the relative stability of the internal environment by regulating the coordinated activities of organs and systems. Homeostasis is the basis for maintaining health and ensuring various physiological functions. Conversely, the occurrence and development of disease is usually accompanied by an imbalance in the body's homeostasis (Qin and Wang, 2022). Major depressive disorder (MDD) is a highly prevalent and debilitating mental disorder with a lifetime prevalence among Chinese adults of 6.9% (Lu *et al.*, 2021). MDD has been identified as one of the leading contributors to global disease burdens (Diseases and Collaborators, 2020). However, its etiology is not yet fully understood, and despite being the focus of more attention in recent years, diagnosis and treatment remain unsatisfactory. Firstly, there are many possible causal factors for MDD, ranging from biological to psychosocial. It is generally believed to be the result of a combination of factors triggering an imbalance in homeostasis throughout the central nervous system. However, most previous studies have explored the pathogenesis of depression from a single dimension without considering the combined effect of multidimensional factors. Secondly, the clinical manifestation varies greatly among individuals and patient groups are highly heterogeneous. MDD remains difficult to diagnose with accuracy in clinical practice and Mitchell *et al*. found that only about 50% of true cases had been diagnosed (Mitchell *et al.,*
2009). Objective indicators of MDD have not been identified and professionals rely primarily on phenomenological descriptions for diagnoses (McCarron *et al.*, 2021; Su and Si, 2022). Finally, the effectiveness of treatment requires improvement. The overall cumulative remission rate was only 67% in the STAR*D study (Rush *et al.,*
2006) and rates of recurrence remain high at 77.1% over the 6-year follow-up (Verduijn *et al*., 2017), partly because objective evaluations of long-term efficacy are lacking and treatments are often based on practical experience (McCarron *et al.,*

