There have been previous cohort studies of depression in China but the PROUD study has a larger scale and improved shareability of cohort data. The PROUD study aims to establish a nationally representative, high-quality, standardized depression cohort and to construct a comprehensive database for facilitation of further analyses and studies. It is hoped to promote the understanding of homeostatic medicine for MDD and facilitate the development of precise diagnoses and treatments, thus filling gaps in current research.

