## Methods and Analysis

### Study design and settings

PROUD is a patient-based, nationally representative multicenter prospective cohort study with baseline and 3-year follow-up assessments. It will be carried out from January 2022 to December 2026 in 52 qualified tertiary hospitals in China, covering 24 provinces and cities: Beijing, Shanghai, Sichuan, Hunan, Hebei, Tianjin, Shandong, Guangdong, Yunnan, Zhejiang, Anhui, Jiangxi, Henan, Shenzhen, Shanxi, Fujian, Hubei, Jiangsu, Liaoning, Heilongjiang, Chongqing, Shaanxi, the Xinjiang Uygur Autonomous Region and the Inner Mongolia Autonomous Region, which are belong to five economic regions in China (Ma, 2009). Multidimensional data, including sociodemographic characteristics, clinical information, biospecimen, neuroimaging, cognitive function, electrophysiology and digital phenotypes, will be collected using standardized operating procedures and uniform equipment to guarantee quality across centers. Ethical approval was obtained from Beijing Anding Hospital, Capital Medical University, Beijing, China. The protocol has been registered in the Chinese Clinical Trial Registry platform (number: ChiCTR2200059053).

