### General inclusion criteria for PROUD

Males and females aged ≥16 years.Inpatients or outpatients with a diagnosis of major depressive disorder based on the Diagnostic and Statistical Manual of Mental Disorders, 5th Edition (DSM-5).Primary school education or above, able to understand the content of the scale.Participation on a voluntary basis and provision of written informed consent.

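### The article calls the cohort representative of the nation and of the Chinese population, but its recruitment frame is consenting, diagnosed patients at tertiary hospitals and does not support that claim

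*Protocol article*

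**What the plan says.** Representativeness is stated in two ways.

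- **As a property of the design.** Study design and settings: "PROUD is a patient-based, nationally representative multicenter prospective cohort study with baseline and 3-year follow-up assessments". The Methods part of the Abstract says the same. The Discussion goes further and drops the patient-based qualifier: "It will recruit a large, multidimensional cohort representative of the Chinese population".
- **As an aim.** Introduction, closing paragraph: "The PROUD study aims to establish a nationally representative, high-quality, standardized depression cohort". The Background part of the Abstract gives the same goal.

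The support offered is size and geography: about 14,000 patients "in 52 qualified tertiary hospitals in China, covering 24 provinces and cities", "which are belong to five economic regions in China".

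The frame is set by these sections:

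- General inclusion criteria: "Inpatients or outpatients with a diagnosis of major depressive disorder based on the Diagnostic and Statistical Manual of Mental Disorders", and "Primary school education or above, able to understand the content of the scale". Participation is voluntary, with written consent.
- General exclusion criteria: other major psychiatric disease, severe medical conditions that preclude participation, and any condition judged unsuitable.
- Participants and eligibility criteria: targets of 4,000 for PMC and 10,000 for NOC. The additional criteria for PMC restrict it to ages 18-65, a HAMD-17 score of at least 14 at screening and baseline, and a period free of antidepressants. NOC takes eligible patients who do not meet the PMC criteria.

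As background, the Introduction cites a study in which "only about 50% of true cases had been diagnosed".

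**The concern.** Representativeness depends on how people come to be in the sample. Numbers and map coverage alone do not supply it. A patient reaches this cohort only by attending a tertiary hospital, having a diagnosis, having some schooling and agreeing to take part. Each of these steps may be related to severity, treatment history and outcome.

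The combined 14,000 has a second feature. Its mix of PMC-type and NOC-type patients follows two recruitment targets, not the mix found among MDD patients in China. The two groups differ by definition in age range, severity threshold and recent treatment, so their outcomes may differ.

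What is at stake is how results are read. Subtype frequencies, hospitalization, conversion to bipolar disorder and the calibration of prediction models all depend on case mix. The article offers the database for further studies, so later users would inherit the label along with the data.

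**Working it through.** **1. The plan's own figure.** PMC 4,000 + NOC 10,000 = 14,000, which matches the stated total. The PMC share, if both targets are met, is 4,000 / 14,000 = 28.6%. The article states no sample size formula, so there is nothing else to reproduce.

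**2. Claim against frame.**

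| Population that could be meant | Does the described frame reach it? |
|---|---|
| The Chinese population (Discussion) | No. The 14,000 are all MDD patients. |
| All people with MDD in China | No. Undiagnosed cases and those not attending tertiary hospitals cannot enter. |
| All diagnosed MDD patients in China | No. Only tertiary hospitals recruit, and schooling and consent are required. |
| Diagnosed MDD patients attending the participating tertiary hospitals | Yes, subject to eligibility and consent. |

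Only the last row is supported by what the article describes.

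**3. Illustration: case mix.** For an unweighted pooled rate,

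bias = (0.286 - true PMC-type share) x (PMC rate - NOC rate).

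The article gives neither the true share nor the rate difference. Both are assumptions here.

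| Assumed rate difference | True share 10% | True share 28.6% | True share 50% |
|---|---|---|---|
| 10 points | +1.9 | 0 | -2.1 |
| 20 points | +3.7 | 0 | -4.3 |

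Example: with assumed rates of 50% in PMC and 30% in NOC, the pooled rate is 0.286 x 50 + 0.714 x 30 = 35.7%. The target is 32% at a true share of 10% and 40% at 50%.

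**4. Illustration: undiagnosed cases.** If the background figure of about 50% diagnosed is assumed to apply here, then for all MDD cases

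bias = (1 - 0.50) x (rate in diagnosed - rate in undiagnosed).

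Assumed differences of 5, 10 and 20 points give 2.5, 5 and 10 points. The sign depends on which group has the higher rate.

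**5. Limits.** Both terms are zero if the rates do not differ, and the first is also zero if the true share is 28.6%. The illustrations show that bias is possible. They do not estimate it.

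**The case against.** The strongest reply has five parts.

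- **The frame is disclosed.** The design section says the study is patient-based, and the Discussion sentence itself goes on to name the tertiary hospitals. This stands as far as it goes: a careful reader can see who is enrolled. It does not rescue the label, because the disclosed frame is what contradicts it.
- **The article condenses a fuller protocol.** Selection of hospitals and patients, and any weighting, may be set out there. Their absence is therefore not part of this point. But even random selection of hospitals would not bring in undiagnosed or non-tertiary patients, so the claim exceeds the frame either way.
- **No national estimate is planned.** The Data analysis section names trajectories, subtypes and prediction models. This stands. A reader might infer that pooled national estimates would be wrong, but no such estimate is specified and bias is not certain.
- **Some outcomes hardly pool.** Early onset needs week 2, and stable response and stable remission need weeks 8 and 12. Table 1 marks these visits as additional for PMC. This also stands: the mix issue bears mainly on outcomes recorded in both cohorts.
- **The 50% figure is background.** The Introduction does not say that it concerns China. This stands, which is why it serves only as an assumption above. Likewise, excluding schizophrenia or bipolar disorder largely defines the MDD population and is weak evidence on its own.

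Two further inferences are tempting and unsupported. A reader might call this a quota sample, but the article gives target sizes and describes no quota mechanism. A reader might also set the illustrated bias against a nominal 95% half-width of 0.83 points (1.96 x sqrt(0.25 / 14,000)) and call it several times larger. That half-width ignores clustering in 52 hospitals of about 269 patients each. With an assumed intracluster correlation of 0.01 to 0.05 it becomes about 1.6 to 3.1 points, and the article gives no value.

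**Conclusion.** The concern holds as a point about a stated property. The article asserts that the cohort is nationally representative, and in the Discussion representative of the Chinese population, while its own sites and eligibility criteria define a narrower group. Unweighted results from the combined 14,000 could be biased if read as national, because the 28.6% PMC share follows the recruitment targets and because non-tertiary and undiagnosed cases are outside the frame.

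The document does not allow the size or direction to be computed. The illustrated ranges (-4.3 to +3.7 points for case mix; 2.5 to 10 points in absolute size for undiagnosed cases) rest on assumed rate differences and on an assumed PMC-type share or diagnosed share. The point does not show that any planned analysis is invalid. Comparisons within the cohort do not require national representativeness. The change is worth making because it alters what the study may conclude.

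**What to change.** 1. In the Abstract (Background and Methods), the closing paragraph of the Introduction, Study design and settings, and the Discussion, replace the representativeness claims with a stated target population, for example: *a multicentre cohort of diagnosed MDD patients attending the participating tertiary hospitals in 24 provinces and cities*.
2. State that descriptive rates will be reported separately for PMC and NOC, and not as an unweighted pooled figure for the country.

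Recruitment, visits and data collection stay as they are. The cost is some rewording, two columns of descriptive results in place of one, and a more modest headline claim.

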## Data Availability

The data generated during the study are not publicly available due to data security and privacy but are available from the corresponding author on reasonable request.
